#### Prior to patient randomization

- Anthropometry (body weight measurement)
- Physical examination
- Measurement of vital signs (BP, HR, RR, to)
- Registration of the concomitant therapy

**Randomization** is the assignment of patients to one of therapeutic groups.

#### After patient randomization

- Sputum sampling (*to study pharmacokinetics of the study/reference product in patients who signed the consent form to take part in the additional part of the study*)
- Handing over the patient diary
- Product dispensing (according to the randomization)

Inhalation of the study/reference product within the study period, including Day 1, should be performed by a patient at home using a jet nebulizer, except for patients who signed the consent form to take part in the additional part of the study to assess DNase concentration in the sputum to evaluate the pharmacokinetics of the medicinal product. These patients will receive an inhalation of the study/reference product at Visit 2 (Day 1) at the hospital using an individual nebulizer.

#### Sputum sampling schedule at Visit 2. Day 1:

- 1 hour  $\pm$  15 min before the inhalation of the study/reference product (*after the patient's randomization*);
- 15 min  $\pm$  5 min after the end of inhalation of the study/reference product;
- 1 hour 45 min  $\pm$  15 min after the end of inhalation of the study/reference product.

The information for patients about the preparation of the study/reference product for the use and the inhalation procedure performed at home will be provided in the Patient Diary.

## **9.2 Visit 3. Day 7 ± 2 days (Week 1)**

- Anthropometry (body weight measurement)
- Physical examination
- Measurement of vital signs (BP, HR, RR, t°)
- Registration of the concomitant therapy
- Spirometry
- Assessment of clinical symptoms of chronic pulmonary disease exacerbation
- Product return and accountability
- Product dispensing
- Handing over the patient diary
- Returning and checking the patient diary
- Assessment of exclusion criteria
- AE reporting

## **9.3 Visit 4. Telephone Call. Day 28 ± 3 days (Week 4)**

- Interviewing a patient about the current condition, concomitant therapy, compliance and assessment of clinical symptoms of chronic pulmonary disease exacerbation (Section 10.6)
- Registration of the concomitant therapy
- AE reporting

## **9.4 Visit 5. Day 56 ± 7 days (Week 8)**

- Anthropometry (body weight measurement)
- Physical examination
- Measurement of vital signs (BP, HR, RR, t°)
- Registration of the concomitant therapy
- Spirometry
- Complete blood count
- Biochemical blood analysis
- Blood test for anti-drug antibodies (IgG, IgE), including neutralizing activity
- Pregnancy test — urine test for chorionic gonadotropin with a test-strip (*for women with preserved childbearing potential*)
- Assessment of clinical symptoms of chronic pulmonary disease exacerbation
- Product return and accountability
- Product dispensing
- Handing over the patient diary

- Returning and checking the patient diary
- Assessment of exclusion criteria
- AE reporting

### **9.5 Visit 6. Telephone Call. Day 84 ± 7 days (Week 12)**

- Interviewing a patient about the current condition, concomitant therapy, compliance and assessment of clinical symptoms of chronic pulmonary disease exacerbation (Section 10.6)
- Registration of the concomitant therapy
- AE reporting

### **9.6 Visit 7. Day 112 ± 7 days (Week 16)**

- Anthropometry (body weight measurement)
- Physical examination
- Measurement of vital signs (BP, HR, RR, t°)
- Registration of the concomitant therapy
- Spirometry
- Pregnancy test — urine test for chorionic gonadotropin with a test-strip (*for women with preserved childbearing potential*)
- Assessment of clinical symptoms of chronic pulmonary disease exacerbation
- Product dispensing
- Product return and accountability
- Handing over the patient diary
- Returning and checking the patient diary
- Assessment of exclusion criteria
- AE reporting

### **9.7 Visit 8. Telephone Call. Day 140 ± 7 days (Week 20)**

- Interviewing a patient about the current condition, concomitant therapy, compliance and assessment of clinical symptoms of chronic pulmonary disease exacerbation (Section 10.6)
- Registration of the concomitant therapy
- AE reporting

### **9.8 Visit 9. Day 168 ± 7 days (Week 24 ± 1 week) (End of Therapy Visit / Early Termination Visit, EOT/ET)**

- Anthropometry (body weight measurement)
- Physical examination
- Measurement of vital signs (BP, HR, RR, t°)
- Registration of the concomitant therapy

- Quality of life assessment according to St. George's Respiratory Questionnaire (version 2.2.)
- Assessment of clinical symptoms of chronic pulmonary disease exacerbation
- Spirometry
- ECG
- Complete blood count
- Biochemical blood analysis
- Urinalysis
- Blood test for anti-drug antibodies (IgG, IgE), including neutralizing activity
- Pregnancy test (*for women with preserved childbearing potential*)
- Product return and accountability
- Returning and checking the patient diary
- AE reporting

## **9.9 Unscheduled Visits**

The patients may be invited to an unscheduled visit at any time during the clinical study at the discretion of the Investigator, including for safety reasons if it is necessary to repeat an examination or procedure. During unscheduled visits, the required procedures, including laboratory and instrumental examinations, will be performed by the decision of the Investigator. Unscheduled visits should be registered in the source documentation and the CRF. Unscheduled visits should not interfere with the scheduled visits provided for by the clinical study protocol.

## **10 STUDY PROCEDURES**

No study-related procedures will be carried out before the volunteer signs the Informed Consent Form. The volunteer will be given sufficient time to fully familiarize himself/herself with the objectives, upcoming study procedures, rights and responsibilities of the study subjects, the risks and benefits of participating in the study, and to discuss the study with family members and/or other physicians.

Below there are the procedures performed in this study. The Investigator should assess all clinical, laboratory, and instrumental tests results (normal values, clinically insignificant deviation, and clinically significant deviation).

### **10.1 Collection of Demographics and Medical History**

During the screening, after signing of the Informed Consent Form, the following demographics and medical history data will be collected from all patients:

- Patient's age (date of birth), sex, race;
- Information on the underlying medical condition — the time of onset of the first symptoms, date of diagnosis establishment; report on physical and instrumental examination findings, including the genotype test results and results of the test for chloride level in the sweat gland secretion;
- Information on the treatment of the underlying medical condition — all prior therapy, including drug-free treatment of CF within 1 year before the Screening, including the earlier applied therapies indicating at least the international nonproprietary and trade names of the medicinal product, route of administration, dosing schedules, course of treatment, and indications;
- Information on the previous and current diseases, including surgeries within 1 year before the Screening;
- Administration of medications, currently and within 4 weeks before the Screening Visit;
- Immunization history (within 1 year before the Screening Visit);
- History of allergies;
- Presence/absence of complaints as of the examination date.

At subsequent visits, the following is assessed:

- Presence/absence of complaints;
- Collection of information about AEs from the previous visit;
- Collection of information about concomitant conditions and medications from the previous visit.

When signing the informed consent, all women (with preserved childbearing potential) and men should also provide consent for observing the adequate contraception methods throughout the study. In this study, adequate contraception methods should be considered the use of methods described in Section 4.2.

## 10.2 Anthropometry

Anthropometry (weight and height measurement) should be performed at the Screening Visit. On Day 1, Day  $7 \pm 2$  days, Day  $56 \pm 7$  days, Day  $112 \pm 7$  days, and Day  $168 \pm 7$  days only weight measurements are taken (APPENDIX 1. Study Procedure Schedule). The body weight will be measured using certified scales, without shoes and outer clothing.

## 10.3 Physical Examination

Physical examination will be performed at the Screening Visit, during treatment on Day 1, Day  $7 \pm 2$  days, Day  $56 \pm 7$  days, Day  $112 \pm 7$  days, and Day  $168 \pm 7$  days in accordance with the Study Schedule (APPENDIX 1. Study Procedure Schedule) to verify the patient's physical parameters and deviations from them, assess the patient's state dynamics, and to reveal AEs/SAEs. Physical examination includes the evaluation of the patient's general condition and the condition of the following:

- skin
- visible mucous membranes

- musculoskeletal system
- subcutaneous fat and lymph nodes
- thyroid gland
- respiratory system
- cardiovascular system
- abdominal cavity organs
- urinary system organs
- sensory organs

Clinically significant differences from the initial examination findings should be regarded as AEs and reported accordingly in the source documentation and in the CRF. Clinically significant conditions revealed at the Screening will be recorded as medical history.

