### 8.2 Visit 1. Screening/Enrollment to Study (Days -21 to -1)

Examination of a patient during the Screening period is carried out for his/her qualification for the study. The Screening period will last up to 21 days. The patients meeting the inclusion criteria based on the examination results during the Screening period will be enrolled in the study.

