## 11.2 Secondary Endpoints

Secondary efficacy endpoints include the comparison of active treatment group (Tigerase) and the reference group (Pulmozyme®) for the following parameters:

- FVC change (absolute %) at Week 24 ± 1 week from baseline (Screening);
- Number of chronic pulmonary disease exacerbations within 24 weeks ± 1 week of therapy;
- The number of days before the development of chronic pulmonary disease exacerbation for a period of 24 weeks ± 1 week of therapy;
- Body weight change at Week 24 ± 1 week from baseline (Screening);
- Change in the average score on the subscales "Symptoms", "Activity", "Impacts", and the average total score of the St. George's Respiratory Questionnaire, version 2.2, at Week 24 ± 1 week from baseline (Screening).

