## 13.2 Adverse Events

The protocol provides for the recording of all adverse events (AEs) observed after the investigational product or reference product administration to the subject and until the subject completes the study.

Patients participating in the study will be carefully monitored for AEs using general surveying, physical and instrumental examinations, and laboratory tests.

Monitoring will be performed in accordance with the Study Procedure Schedule (APPENDIX 1. Study Procedure Schedule). The adverse events will be classified and entered on the Case Report Form. The classification will be carried out according to the following parameters: seriousness, intensity, causality to the medicinal product, body system, organ and organ system, outcome, actions in relation to the investigational product, and measures taken. The classification will be carried out by the Principal Investigator in accordance with the definitions below.

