### **Analysis of secondary efficacy endpoints**

In this study, the planned secondary efficacy endpoints include the following:

- FVC change (absolute %) at Week 24  $\pm$  1 week from baseline (Screening);
- Number of chronic pulmonary disease exacerbations within 24 weeks  $\pm$  1 week of therapy;
- Number of days to a chronic pulmonary disease exacerbation over the period of 24 weeks  $\pm$  1 week of therapy;
- Body weight change at Week 24  $\pm$  1 week from baseline (Screening);
- Change in the average score on the subscales "Symptoms", "Activity", "Impacts", and the average total score of the St. George's Respiratory Questionnaire, version 2.2, at Week 24  $\pm$  1 week from baseline (Screening).

To analyze the change in FVC on Week 24  $\pm$  1 week versus baseline, a t-test or a Mann–Whitney test will be used, depending on the type of data distribution.

To analyze the number of chronic pulmonary disease exacerbations within 24 weeks  $\pm$  1 week of the therapy, Poisson regression is suggested. For each group of patients, the average number of exacerbations ( $M \pm SD$ ) recorded for 24 weeks  $\pm$  1 week will be presented. Subject's gender, age, FEV1 baseline (40–60% or more than 60% to 100% of the due value), presence of concomitant diseases, etc., can be used as covariates.

Additionally, the number and proportion of patients with one, two or three, or more exacerbations will be tabulated in total and by baseline FEV1 stratification. The intergroup comparison of these data will be performed by the  $\chi^2$ -criterion or Fisher's exact test (if the expected frequency in any cell is less than 5). The number of days to chronic pulmonary disease exacerbation will be analyzed using the Kaplan–Meier method, and also using the Cox regression model.

The intragroup analysis of body weight change at Week 24  $\pm$  1 week compared to baseline will be performed using the paired t-test or Wilcoxon test (with significant deviations from a normal distribution). The intergroup comparison will be performed using the t-test or Mann–Whitney test.

The data on change of the average score of the subscales "Symptoms", "Activity", "Impacts", and the average total score of the St. George's Respiratory Questionnaire, version 2.2, at Week 24  $\pm$  1 week compared to baseline will be analyzed using non-parametric methods: Wilcoxon test — for intragroup comparison and Mann–Whitney test — for intergroup comparison.

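### Body weight change is measured from Screening although a pre-randomisation Day 1 weight exists, and Sections 10.3 and 10.4 judge adverse events against an undefined initial examination that does not fit Section 13.2

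*Protocol*

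**What the plan says.** **Timing.** Section 8.2 states: "The Screening period will last up to 21 days". Section 9.1 lists weight, physical examination and vital signs at Visit 2 (Day 1) under the heading "Prior to patient randomization", hence before the first inhalation.

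**Weight endpoint.** Section 11.2 fixes the reference visit: "Body weight change at Week 24 ± 1 week from baseline (Screening". The Protocol Summary and Section 15.1 say the same. For the analysis within each arm, Section 15.1 says that weight change "compared to baseline will be performed using the paired t-test or Wilcoxon test". Between arms it says: "The intergroup comparison will be performed using the t-test or Mann–Whitney test".

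**Adverse events from examination and vital signs.** Sections 10.3 and 10.4 both state: "Clinically significant differences from the initial examination findings should be regarded as AEs and reported accordingly in the source documentation and in the CRF". Neither says which visit is the initial examination. Both list Day 1 among the assessments made during treatment. Section 10.3 sends to medical history only the conditions found at Screening.

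**Adverse events in general.** Section 13.2 records events "observed after the investigational product or reference product administration to the subject", and Section 13.2.1.1 defines an adverse event as something identified after administration. Appendix 1 has no adverse event registration at Visit 2; the first is at Visit 3. Section 13.2.13 has a clear rule for laboratory values: clinically significant deviations found at or after Screening are medical history, and only new or worsening ones after dosing are adverse events. Its title mentions vital signs, but its text covers laboratory results only.

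**The concern.** When a measurement is repeated just before the first dose, the later value is normally the better reference, because nothing before it can be due to treatment. The plan takes these measurements and then does not use the Day 1 weight as baseline. The within-arm weight result therefore mixes up to three weeks of pre-treatment change with the effect of 24 weeks on product.

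The adverse event wording is a different kind of problem. Site staff classify findings from the protocol text while the study runs, so an unclear reference cannot be repaired later in an analysis plan. If staff take the initial examination to be Screening, a sign that appeared in the screening period and persists at Visit 3 can be recorded as an adverse event. Section 15.1 compares adverse event frequencies, and abnormalities on examination and vital signs, between arms. The study is open-label (Section 3.2.1.2), so staff applying an unclear reference know which product the patient receives.

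**Working it through.** The protocol gives no power, sample size or error rate for weight or adverse events, so there is no figure of its own to reproduce on this point. The check is day-counting, a small simulation and a comparison of sections.

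**1. Share of the weight interval that precedes treatment**

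Inputs: Screening on Day -21 to Day -1 (Section 8.2); first inhalation on Day 1 (Section 5.5); Visit 9 on Day 168 ± 7 (Section 9.8). The schedule has no Day 0, so Day -21 to Day 1 is 21 days and Day 1 to Day D is D - 1 days.

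Share = 21 / (21 + D - 1)

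- D = 161: 21 / 181 = 11.6%
- D = 168: 21 / 188 = 11.2%
- D = 175: 21 / 195 = 10.8%

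If Screening is on Day -1, the share at Day 168 is 1 / (1 + 167) = 0.6%. With the Day 1 weight as reference it is zero.

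**2. What a pre-treatment drift does to the two weight tests**

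Assumptions, none of them from the protocol: the same mean drift in both arms before Day 1, SD 1 kg for change before Day 1, SD 2.5 kg for change after it, independent normal changes and no treatment effect. From the protocol: 50 patients per arm. I ran 4,000 simulations with two-sided t-tests at 0.05.

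| Common drift before Day 1 (kg) | Within-arm rejection | Between-arm rejection |
|---|---|---|
| 0 | 5% | 5.1% |
| 0.3 | 12% | 5.2% |
| 0.5 | 27% | 5.5% |
| 1.0 | 74% | 5.2% |

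The within-arm test reacts to drift that has nothing to do with treatment. The between-arm test stays near 5%, because both reference visits precede randomisation.

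Added noise under the same assumptions: the SD of change from Screening is √(1² + 2.5²) = √7.25 = 2.69 kg, against 2.5 kg from Day 1. The ratio is 2.69 / 2.5 = 1.08, or about 8% wider.

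**3. Adverse event wording, section by section**

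| Section | How it treats Day 1 or pre-dose findings |
|---|---|
| 9.1 | Day 1 examination and vital signs come before randomisation |
| 10.3, 10.4 | Day 1 is listed as during treatment; differences from an unnamed initial examination are adverse events |
| 10.3 | Only conditions found at Screening go to medical history |
| 13.2 | Only events after administration are recorded |
| 13.2.1.1 | Adverse event if identified after administration; conditions from before the study began count only if they change |
| 13.2.13 | Pre-dose deviations go to medical history, but for laboratory values only |
| Appendix 1 | No adverse event registration at Visit 2 |

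Take a finding absent at Screening, present on Day 1 before dosing and still present at Visit 3. It was not found at Screening, so the medical history sentence in 10.3 does not cover it. Whether it existed before the study began is unclear, since the patient was already enrolled at consent (Section 8.1). At Visit 3 it differs from the Screening examination, and it is again seen after administration. Read literally, 10.3 can make it an adverse event, while the principle in 13.2.13 would make it medical history.

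**4. Time at risk of this at Visit 3 (Day 7 ± 2), with Screening on Day -21**

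- Day 5: 21 / (21 + 4) = 84%
- Day 7: 21 / (21 + 6) = 78%
- Day 9: 21 / (21 + 8) = 72%

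These are shares of calendar time in the worst case, not shares of events.

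**The case against.** On weight, Screening is stated openly and is also the baseline for FEV1, FVC and the St. George's questionnaire, so one visit serves all the change endpoints. The randomised comparison is what matters, and it is not biased. Both statements are correct. They limit the consequence to the within-arm test and some precision, but they are no reason to set aside a better measurement that is already planned.

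On adverse events, a reader might infer that the plan makes Screening the reference, or that a finding first made on Day 1 before dosing becomes an adverse event. The documents do not support either. Sections 10.3 and 10.4 name no visit; Screening is a plausible reading, no more. Sections 13.2 and 13.2.1.1 and Appendix 1 exclude a finding first made at the pre-dose visit. Other safeguards also help. At later visits, adverse event information is collected since the previous visit (10.1), an onset date is required (13.2.3), causality considers timing (13.2.5), and exclusion criterion 2 bars acute respiratory infection or exacerbation in the 4 weeks before and during Screening. These make misclassification less likely. They do not settle the persisting finding worked through above, and no section says that 13.2 overrides 10.3 and 10.4.

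It is also tempting to say that the Day 1 data are never used, or that a true difference in adverse events would be diluted. The first goes too far: the over-time analysis of vital signs in 15.1 does not exclude Day 1. The second cannot be quantified from the protocol.

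**Conclusion.** Two limited points stand.

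- **Weight.** The stated baseline lets up to 21 of 188 days (11%) of pre-treatment change into the endpoint. The within-arm paired test can be distorted: under the assumed SDs, a common drift of 0.5 kg raises its rejection rate from 5% to 27%. Some noise is added. The comparison between products is not biased. The 11% assumes Screening on Day -21, and the effect shrinks as the gap shortens.
- **Adverse events.** Sections 10.3 and 10.4 conflict with 9.1, 13.2, 13.2.1.1 and Appendix 1 because the reference examination is not named and Day 1 is listed as during treatment. A change that arises between Screening and Day 1 and persists at Visit 3 could be counted as an adverse event. The number of such cases cannot be estimated from the protocol; the 72% to 84% is only a worst-case share of time.

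**What to change.** 1. In Section 11.2, Section 15.1 and the Protocol Summary, define baseline body weight as the Day 1 pre-randomisation weight, with the Screening weight used if it is missing.
2. In Sections 10.3 and 10.4, replace the unnamed initial examination with the last examination before the first dose, that is the Day 1 pre-randomisation assessment, and stop listing Day 1 as during treatment.
3. Extend the rule in 13.2.13 to physical examination and vital signs: pre-dose findings go to medical history, and only new or worsening clinically significant findings after dosing are adverse events.
4. Keep Screening as baseline for spirometry, laboratory tests, ECG and the St. George's questionnaire, which are not repeated on Day 1.

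The cost is a few sentences and a note on completing the case report form, with no new assessments. The small downside is that weight will have a different baseline visit from spirometry and the questionnaire, which the tables should state.

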#### **10.4 Vital Signs**

Vital signs assessment will include measurement of the following:

- systolic blood pressure (SBP)
- diastolic blood pressure (DBP)
- heart rate (per minute) (HR)
- respiratory rate (per minute) (RR)
- body temperature in the armpit (t°)

Vital signs are assessed at the Screening Visit, during treatment on Day 1, Day 7 ± 2 days, Day 56 ± 7 days, Day 112 ± 7 days, and Day 168 ± 7 days (APPENDIX 1. Study Procedure Schedule).

The body temperature should be measured by the same method (axillary temperature). When measuring blood pressure, heart rate, and respiratory rate (after 5 minutes of rest), the patient should be in a sitting or reclining position.

Clinically significant differences from the initial examination findings should be regarded as AEs and reported accordingly in the source documentation and in the CRF.

